##### Optional study components requiring consent

Participants able to attend MBCIU in Parkville, VIC may provide additional consent to partake in the neuroimaging component of the study. The study PICF will contain a separate consent section specific to this component. A PICF supplied by Services Australia will be required for participants who wish to provide their Medicare Benefits Scheme (MBS) and Pharmaceutical Benefits Scheme (PBS) data to be used as part of the health economic evaluation of the study (see the Study procedures, Explatory procedures section). In addition, participants may provide extended consent for their study data to be shared to future projects that are ‘(1) an extension of, or closely related to, the original project; or (2) in the same general area of research (eg, genealogical, ethnographical, epidemiological or chronic illness research)’.^26^ These projects must have received approval from a registered HREC committee. Data will be shared in a non-identifiable format where possible.

### Intervention

#### Therapy arm

Therapy will consist of 16 sessions delivered by a psychologist via Telehealth or face-to-face at the Austin Hospital. The first session will be 90 min, whereas follow-up sessions will be 60 min. Sessions will be delivered weekly as much as possible; however, participants will have 20 weeks to complete all 16 sessions to accommodate for cancellations.

The therapy is a hybrid, based on principles of ACT, but including several elements from Cognitive Behavioural Therapy. Delivery is guided by a purpose-written therapist manual and corresponding participant workbook. Development of the therapy, including patient involvement and integration of their feedback can be read in detail here ([name] *et al*, in submission). Manualised modules include (1) education on concepts of health and illness and the neurobiology of symptom experience in DSCATT, (2) core principles of ACT, (3) evaluating the daily routines, (4) increasing levels of activity, (5) identifying and connecting with values, (6) setting goals, (7) strategies for managing uncertainty of illness. Additional modules on self-compassion, improving sleep, addressing difficulties with thinking and memory, and navigating social relationships will be administered according to participant need. See online supplemental table S1 for an outline of content covered in each session.

Trial clinicians will have the capacity to flexibly adapt individual sessions to suit the presenting needs of participants. The participant will decide which is the most pressing issue/problem for them. This will guide the order of delivery of modules between session 6 and 10, contingent on where the participant is currently at in their therapy trajectory.

Participants will be provided with homework tasks each week via email, to be completed between sessions to practise introduced skills and concepts. They will be encouraged to set aside up to 1 hour per week to complete these tasks. Homework worksheets provided to the participants are included in the participant workbook. A reminder email or SMS, based on the participants’ communication preferences, will be delivered during the week to follow-up on homework tasks. A review of homework tasks will be performed each session, including whether the participant completed the set homework and discussion of progress and any challenges experienced.

Treatment adherence (visits attended) will be recorded by the trial therapists. Therapist notes detailing modules addressed in session, homework completed and risk assessment, as per standard clinical practice, will be recorded.

Following completion of the Week 32 questionnaires, trial therapists will contact their participants via telephone to discuss ongoing progress, and answer queries or concerns the participant may have following the cessation of the intervention.

##### Trial therapist eligibility

Sessions will be delivered by Australian Health Practitioner Regulation Agency-registered psychologists (clinical, health or neuropsychologists) who have completed additional training in ACT.

### Waitlist control arm

Individuals who are assigned to the waitlist control group will be encouraged to continue their treatments as usual. They will be sent study questionnaires at Baseline, and 10, 20 and 32 weeks postrandomisation. In addition, the project coordinator will telephone participants at Week 10 and Week 20 to review the occurrence of adverse events (AEs) (to serve as a comparator to the therapy arm). After completion of the Week 32 questionnaires, participants will be offered access to the 16-session therapy, if desired. If they choose to proceed, they will be sent additional study questionnaires to complete 10 weeks and 20 weeks after commencing their first therapy session.

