### Secondary aims

Examine the effects of the therapy on participants’ health and well-being, and its safety profile (see table 2).

**Table 2 T2:** Clinical, safety and exploratory outcomes

Area	Measure	Timepoint
Clinical		
Quality of life	Assessment of Quality of Life 8-dimension scale (AQoL-8D)^42 43^	Baseline, Week 10, 20 and 32
Functioning	Work and Social Adjustment Scale (WSAS)^44^	Baseline, Week 10, 20 and 32
Depression, anxiety and stress symptoms	Depression, Anxiety and Stress Scale 21 (DASS-21)^45^	Baseline, Week 10, 20 and 32
Severity of illness and perceived improvement	Patient Global Impression scale (PGI)—severity and improvement^46 47^	Baseline (severity subscale only), Week 10, 20 and 32
Physical symptoms	30-item participant self-report Debilitating Symptom Complexes Attributed to Ticks (DSCATT) symptom scale developed by our research group	Baseline, Week 10, 20 and 32
Psychological flexibility	Comprehensive assessment of Acceptance and Commitment Therapy processes (CompACT)^48^	Baseline, Week 20 and 32
Clinician* rated severity of illness and perceived improvement	Transdiagnostic Clinical Global Impression (T-CGI) scale^49^	Baseline (severity subscale only), and treatment endpoint, that is, after completion of the participants 16th treatment session
Safety		
Safety of the intervention	Adverse events, as reported by the participant, and/or as observed by study staff	Assessed at each session by trial therapists; assessed at Week 10 and Week 20 by project coordinator (waitlist controls)
	Negative Effects Questionnaire (NEQ)—20 item^28^	Postintervention (Week 20) for therapy randomised, and treated waitlist controls
Exploratory		
Preliminary cost-effectiveness of the intervention	Healthcare resource use and cost, and lost productivity (absenteeism and presenteeism). Obtained via participant self-report on a tailored resource use questionnaire (RUQ) and supplemented by Medicare Benefits Scheme/Pharmaceutical Benefits Scheme (MBS/PBS) data from Services Australia (where specific consent is provided to access this data).	Baseline, Week 20 and Week 32 (RUQ); MBS/PBS data obtained for 3 months prior to randomisation (to reflect the same reporting time frame as RUQ) up until 8 months post randomisation
Brain activity	Task-based (emotional Stroop) and resting-state fMRI Blood Oxygen Level Dependent (BOLD) signal	Baseline and post-treatment (20 weeks after completion of the intervention)

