#### Safety monitoring

Our definition, assessment and recording of AEs and harms of treatment will be informed by Klatte *et al*^29 30^ and the National Health and Medical Research Council (NHMRC) safety monitoring and reporting guidelines.^31^ AEs may include worsening of pre-existing symptoms, recurrence of previous symptoms not present/disclosed at randomisation, diagnosis of a new medical condition and/or emergence of new symptoms or injuries.

The occurrence of AEs in participants randomised to receive the therapy will be reviewed by the trial therapists during each treatment session and documented in REDCap as necessary. AEs will include those reported by the participant and those observed by the trial therapist. The severity and causality of events to the therapy, and other study procedures, will be rated by both the participant and the medical monitors. The medical monitors will be unblinded to group allocation so details of the participants progress in therapy can be discussed (as relayed by the participant’s trial therapist) and ascertained if related to the AE. Waitlist control participants will be telephoned at Week 10 and Week 20 by the project coordinator to determine the occurrence of AEs. All AEs will be followed up until stable/resolved. Verbal consent will be required from the participant to be followed up if AEs persist at Week 32.

All safety reporting in the study will follow the Sponsor’s (Austin Health) current safety reporting guidelines.

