#### Safety outcomes

AEs will be summarised descriptively by treatment group, including the number of AEs and the number of participants with at least one AE. Summary statistics will be presented for the full measure and for each of the factors of the NEQ.

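### Adverse events are sought at up to 16 therapy sessions in one arm and in two telephone calls in the other, so the planned by-arm adverse event figures are not comparable

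*Protocol article*

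**What the plan says.** The protocol article sets two different AE enquiries for Weeks 0 to 20.

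- **Therapy arm** (Safety monitoring): "The occurrence of AEs in participants randomised to receive the therapy will be reviewed by the trial therapists during each treatment session". Events come from two sources: "AEs will include those reported by the participant and those observed by the trial therapist". The Therapy arm section gives the number and window of sessions: "participants will have 20 weeks to complete all 16 sessions to accommodate for cancellations".
- **Waitlist arm** (Safety monitoring): "Waitlist control participants will be telephoned at Week 10 and Week 20 by the project coordinator to determine the occurrence of AEs". The Waitlist control arm section gives the purpose of the calls, which is to "review the occurrence of adverse events (AEs) (to serve as a comparator to the therapy arm".

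Table 2 (Secondary aims) repeats the split: "Assessed at each session by trial therapists; assessed at Week 10 and Week 20 by project coordinator (waitlist controls".

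The AE definition is broad: "AEs may include worsening of pre-existing symptoms, recurrence of previous symptoms not present/disclosed at randomisation", and it extends to new symptoms, new diagnoses and injuries. The case definition in Table 3 notes that symptoms change in kind and strength within a person.

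The planned analysis (Safety outcomes) is: "AEs will be summarised descriptively by treatment group, including the number of AEs and the number of participants with at least one AE". The article describes no AE enquiry common to both arms and attaches no caveat to the comparison.

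**The concern.** Closer monitoring of people in therapy is reasonable. The difficulty is that two unlike enquiries are declared comparable and set side by side. The arms differ in how often participants are asked, in how far back they must remember, in who asks, and in whether a therapist's own observations feed the count.

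The two chosen summaries, the number of events and the number of people with any event, are sensitive to these differences. A short symptom flare is likely to be recorded when someone asks the following week and may be lost when the question comes up to ten weeks later.

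What is at stake is how the safety table will be read. An apparent excess in the therapy arm could reflect asking rather than harm, and a real excess could be dismissed on the same ground. In a field where the authors themselves note controversy over psychological treatment, either misreading could affect the decision on a larger trial.

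**Working it through.** The protocol gives no AE rate and no AE precision figure, so there is no stated number to reproduce on this point.

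**Step 1. Count the enquiries.** From the Therapy arm and Safety monitoring sections, the therapy arm has up to 16 and the waitlist has 2, a ratio of 16/2 = 8. If 16 sessions spread evenly over 20 weeks, the mean interval is 20/16 = 1.25 weeks, against 20/2 = 10 weeks.

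**Step 2. Illustrate the effect on counts.** Assumptions, none from the protocol: equal true AE rates in both arms, constant over 20 weeks; each AE is a point event; the chance that it is reported at the next enquiry halves every h weeks. Mean capture over an asking interval of w weeks is

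f(w) = (1 − 2^(−w/h)) × h / (w × ln 2).

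Two therapy schedules are compared with f(10) for the waitlist:

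- A: sessions spread over 20 weeks, capture f(1.25).
- B: weekly sessions ending at Week 16 with no enquiry afterwards, capture (16/20) × f(1). The Therapy arm section aims for weekly sessions and allows 20 weeks only for cancellations, so B is what a fully attending participant would follow.

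| h (weeks) | f(10) waitlist | A: f(1.25) | Ratio A | B: 0.8 × f(1) | Ratio B |
|---|---|---|---|---|---|
| 2 | 0.28 | 0.81 | 2.9 | 0.68 | 2.4 |
| 4 | 0.48 | 0.90 | 1.9 | 0.73 | 1.55 |
| 8 | 0.67 | 0.95 | 1.4 | 0.77 | 1.15 |
| 16 | 0.81 | 0.97 | 1.2 | 0.78 | 0.96 |

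Worked line for h = 16, schedule B: f(1) = (1 − 2^(−1/16)) × 16/0.693 = 0.979; 0.8 × 0.979 = 0.78; 0.78/0.81 = 0.96.

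**Step 3. Participants with any AE.** Assume further 2 true events per person in 20 weeks, Poisson distributed, so the share is 1 − exp(−2 × capture).

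- h = 2: 80% (A) or 74% (B), against 43% in the waitlist.
- h = 16: 86% (A) or 79% (B), against 80% in the waitlist.

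**Step 4. Allow for early leavers.** Suppose 40% stop after 8 weekly sessions and are not asked again. This is an assumption, the complement of the 60% retention used as an illustration under Sample size estimation. The therapy factor 0.8 in B becomes 0.6 × 16/20 + 0.4 × 8/20 = 0.64. The ratios are then about 1.9, 1.2, 0.92 and 0.77 for h = 2, 4, 8 and 16.

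With no true difference, the count ratio therefore ranges from well above 1 to below 1, depending on recall, session timing and drop-out.

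**The case against.** **The direction is not settled.** A reader might infer that the therapy arm is bound to show more AEs. The documents do not support that. Schedule B and early leaving can bring the ratio to 1 or below, and participants may under-report to their own therapist. This objection stands. Inflation of mild, transient events in the therapy arm is probable, not certain.

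**The size rests on assumptions.** The half-lives and event rate are not in the protocol, and the model treats every AE as forgettable. A new diagnosis or a lasting deterioration would often be recalled at ten weeks, and serious events are probably least affected. This stands too, so the figures are only a range.

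**Safety has other sources.** A reader might infer that the whole safety aim rests on this table, or that waitlist AEs are purely self-reported. Neither holds. Table 2 adds the Negative Effects Questionnaire and allows for staff observation of AEs in general, and AEs are rated for severity and causality. However, that questionnaire goes only to treated participants and the medical monitors are unblinded, so neither supplies a like-for-like comparison between arms.

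**The table is descriptive, in a feasibility trial.** No test is planned, safety is a secondary aim, and the trial is not designed to detect a treatment effect. This lowers the severity. It does not remove the problem, because the protocol itself calls the waitlist calls a comparator.

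**The analysis plan could handle it.** It can change the table layout and add a caveat. It cannot create an equal enquiry that was never made.

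**Conclusion.** The concern holds as a moderate design and reporting fault. The schedules, the declared comparator role and the by-arm tabulation are all in the protocol, and together they give AE figures that cannot be compared between arms.

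Illustrative count ratios under equal true rates are about 2.9 to 1.2 (sessions spread over 20 weeks) or 2.4 to 0.96 (weekly sessions ending at Week 16). Both ranges assume recall half-lives of 2 to 16 weeks and full attendance; early leaving lowers the ratios further. The protocol supports neither a definite direction nor a definite size. Retention, the primary outcome, is unaffected.

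**What to change.** 1. Base the between-arm harm comparison on data collected identically in both arms: the proportion rating themselves worse on PGI-improvement, and worsening on the DSCATT symptom scale, at Weeks 10, 20 and 32. Table 2 already schedules both.
2. For participants not yet past those visits, add one identical AE item, with the same recall period, to the REDCap questionnaires that both arms already receive at Weeks 10 and 20.
3. Report session-detected AEs in a separate single-arm table for therapy recipients. Session monitoring itself does not change.
4. Remove the comparator description from the unequally collected data.

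Items 1, 3 and 4 need only changes to wording and table shells. Item 2 needs an ethics amendment and possibly re-consent, and makes the questionnaire slightly longer. Because recruitment was planned from June 2023, it would not cover participants already past Week 10 or Week 20. These measures equalise the enquiry, but they remain self-report by participants who know their allocation, and the two scales capture worsening rather than new diagnoses or injuries.

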### Standard care and addition to standard care

While there is no defined standard care for DSCATT at present, the therapy and study procedures will be completed alongside participants’ treatment as usual. This includes medication, vitamins, herbal remedies and complementary therapies they may be using. However, participants will not be permitted to employ other psychological therapies while they are completing the 16-session trial therapy. They may use other psychological therapies after they complete the intervention, if desired, or if they are randomised into the waitlist control arm. Candidates who are screened for the study and already employing psychological therapies as part of their standard care will be encouraged to discuss the potential of pausing these therapies with their current healthcare provider(s) prior to randomisation into the trial.

Participants’ concomitant treatment throughout the trial will be determined via a self-report resource use questionnaire (RUQ) provided at baseline, Week 20 and Week 32. This will be supplemented via MBS and PBS data retrieval where participant consent is provided.

### Study procedures

See figure 1 for study schema which outlines procedures following informed consent.

**Figure 1 F1:**
[figure not shown]
Study procedures following informed consent. ^∧^Project coordinator contacts participant at Week 10 and Week 20 to review for AEs; *AEs reviewed by trial therapist in each treatment session, T-CGI completed by trial therapist pretreatment and post-treatment programme; **treatment programme participants only. Note: self-report questionnaires (during the RCT phase) will be administered at baseline (prior to randomisation), 10 weeks, 20 weeks and 32 weeks postrandomisation (irrespective of what session number the therapy randomised participants are up to in the treatment programme). ^#^Primary endpoint; ^~^follow up timepoint. Neuroimaging at the Melbourne Brain Centre Imaging Unit, Parkville, optional for participants (treatment group and treated waitlist group) to complete prior to commencing the treatment programme and repeated 20 weeks later/after their 16th therapy session—not shown on figure. ACT, Acceptance and Commitment Therapy; AE, adverse event; AQoL-8D, Assessment of Quality of Life-8 dimension; CBRQ-S, Cognitive Behavioural Response Questionnaire (short version); CEQ, Credibility/Expectancy Questionnaire; CompACT, Comprehensive assessment of Acceptance and Commitment Therapy processes; DASS-21, Depression Anxiety Stress Scale, 21 item; DSCATT, Debilitating Symptoms Complexes Attributed to Ticks; MINI, Mini International Neuropsychiatric Interview; NEQ, Negative Effects Questionnaire; PGI-S/I, Patient Global Impression scale (severity and improvement); RUQ, resource use questionnaire; SRQs, self-report questionnaires; T-CGI, transdiagnostic Clinical Global Impression scale; tx WL, treated waitlist; WSAS, Work and Social Adjustment Scale.

#### Screening

Following written, informed consent, participants will be assessed by a physician who will review their medical history, confirm the presence of DSCATT and ensure the participant meets the remaining eligibility criteria (see table 3). Participants’ medical records held by other healthcare providers will be requested as necessary (as specified on the PICF). In addition, the trial physician may order investigations to confirm eligibility (for example, to rule out a medical condition which may better explain their symptoms) on an as-needed basis, with results shared with their treating team. The MINI International Neuropsychiatric Interview (V.7.0.2)^27^ will be administered at this visit. If eligible and willing to proceed, participants will be randomised into the trial by the project coordinator (see the Randomisation section).

#### Study questionnaires

Participants will be sent a suite of questionnaires via REDCap at baseline (prior to randomisation into the therapy/waitlist control arm); and 10 weeks, 20 weeks (primary endpoint) and 32 weeks (follow-up) after randomisation (and irrespective of which session number the participant has completed in the treatment programme). These questionnaires will assess quality of life, general functioning, disability and impairment, physical symptoms, views about illness and healthcare utilisation (refer to the Outcomes section for further details). All participants who partake in the treatment programme (randomised participants and waitlist controls) will be provided with a treatment satisfaction questionnaire and the 20-item Negative Effects Questionnaire (NEQ)^28^ 20 weeks after commencing the therapy to ascertain its acceptability and safety.

#### Feedback interview

All participants who partake in the treatment programme (randomised participants and treated waitlist controls) will be invited to attend a feedback interview with the project coordinator after they have completed their final session (note, participants who are withdrawn prematurely from the trial may also attend this interview if desired). The project coordinator will follow a semi-structured interview guide (see online supplemental material ‘feedback interview guide’) to explore the participant’s views and experiences of the treatment, including perceived value of the therapy. The interview will be audio recorded, transcribed verbatim (names omitted) and then analysed following qualitative analysis methods.

#### Safety monitoring

Our definition, assessment and recording of AEs and harms of treatment will be informed by Klatte *et al*^29 30^ and the National Health and Medical Research Council (NHMRC) safety monitoring and reporting guidelines.^31^ AEs may include worsening of pre-existing symptoms, recurrence of previous symptoms not present/disclosed at randomisation, diagnosis of a new medical condition and/or emergence of new symptoms or injuries.

The occurrence of AEs in participants randomised to receive the therapy will be reviewed by the trial therapists during each treatment session and documented in REDCap as necessary. AEs will include those reported by the participant and those observed by the trial therapist. The severity and causality of events to the therapy, and other study procedures, will be rated by both the participant and the medical monitors. The medical monitors will be unblinded to group allocation so details of the participants progress in therapy can be discussed (as relayed by the participant’s trial therapist) and ascertained if related to the AE. Waitlist control participants will be telephoned at Week 10 and Week 20 by the project coordinator to determine the occurrence of AEs. All AEs will be followed up until stable/resolved. Verbal consent will be required from the participant to be followed up if AEs persist at Week 32.

All safety reporting in the study will follow the Sponsor’s (Austin Health) current safety reporting guidelines.

